### Statistical methods

#### Statistical analysis

Statistical methods using statistical analysis software SPSS21.0 will be used to analyze the test results. In the descriptive analysis of samples, the continuous variables are expressed in mean and standard deviation for the data of normal distribution and in the range of median and quartile for the data of non-normal distribution. The normally distributed packets are compared statistically between the *t* test groups. The ordinal level variables of the non-normal distribution are compared statistically with the Mann-Whitney *u* test. Measures with discrete distributions will be expressed as percentages and analyzed using accurate tests of either chi-square *Χ*^2^ or Fisher, as appropriate. If necessary, we will use the general linear model or logit model to adjust for confounding effects.

We will use the *t* test or the Mann-Whitney test to compare baseline characteristics between the different groups. If there is statistical significance, inequality will be treated as a confounding factor in the final efficacy analysis. In order to compare one-time or two-time results between groups, the continuous data will be analyzed by *t* test or non-parametric test, and the data will be analyzed by Pearson chi-squared or Fisher precision test. In order to control the possible confounding variables, linear models or linear regression models will be used for dependent continuous variables and dependent classified variables. The subgroup analysis of the main results will be stratified according to the sex of the participants. Analysis of variance will be used to repeat the measurement data. The analysis of primary and secondary outcomes will be based on intention-to-treat (ITT) and a per-protocol (PP) basis. The results of the ITT analysis will be compared with those of the PP analysis to determine if they are consistent. The missing data will be treated as the last carrier of observation. Adverse events will be listed and analyzed using either a chi-square test or Fisher’s precision test.

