Sedatives, anesthetics, psychoactive drugs, muscle relaxants, or Na+ and Ca2 + channel blockers, such as carbamazepine, will be administered during the evaluation period.The patient relies on inhalers.The course of disease is more than 1 year.There are any contraindications, such as pacemaker, denture, and metal prosthesis.There is an epilepsy or seizure history confirmed by EEG.Serious diseases such as heart, liver, and kidney failure.Progressive nervous system diseases, such as the central nervous system or degenerative diseases.The patient has a fever.The patient has a local skin injury or inflammation. The patient has hemostasis, coagulation, or anticoagulation dysfunction. Acute large area cerebral infarction. High sensitivity of pain stimulation area. Brain injury, brain parasitosis, or brain tumor. Hemiplegia or dysfunction of limbs (patients with a Fugl-Meyer scale score below 85). Accompanied by aphasia. Patients with incomplete clinical data and poor compliance. Accompanied with serious organ disease, endocrine disease, and mental illness. Patients with a score of 10 or more on the PHQ-9 scale.

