### Trial outcomes

#### Outcome measures

In this study, primary outcomes will be measured at baseline and at the end of every week from the 1st to the 4th week. Secondary outcomes will be measured at baseline and the end of the 4th week. During each treatment, adverse events and untoward effects will be assessed. All outcome assessments will be independently performed by experienced and blinded assessors, the same one professional rehabilitation physician. A summary of all the measures in the trial is shown in Table 1.

**Table 1 Tab1:** Data on the design of the study

Point in time	Screening stage	Treatment period 1 (1 week)	Treatment period 2 (2 weeks)	Treatment period 3 (3 weeks)	Treatment period 4 (4 weeks)
Informed consent	**×**				
Inclusion and exclusion criteria	**×**				
Withdrawal, drop out, and termination criteria		**×**	**×**	**×**	**×**
Basic information	**×**				
Past medical history	**×**				
Therapeutic parameter record		**×**	**×**	**×**	**×**
**(*****Baseline*****) Fatigue Severity Scale (FSS)**	**×**	**×**	**×**	**×**	**×**
**Functional Assessment Chronic Illness Therapy (Fatigue) (FACIT-F)**	**×**				**×**
**Fatigue Impact Scale (FIS)**	**×**				**×**
**Specialized Quality of Life Scale in Stroke (SS-QOL)**	**×**				**×**
Overall efficacy evaluation					**×**
Complications	**×**	**×**	**×**	**×**	**×**
**Adverse events recorded**	**×**	**×**	**×**	**×**	**×**

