### Study endpoints

The endpoints of the study are as follows:
In the event of a serious adverse reaction during the course of the test, the test will be terminated in time to protect the subject.In the event of a serious complication or deterioration in the course of the test, the test will be terminated.The test will be terminated if the subject is asked to withdraw from the clinical study.And if the patient does not cooperate and does not receive treatment and the therapist’s explanation is not working, then the study will be suspended.

The researchers will keep detailed records of why and when the subjects quit the study.

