### Sample size

The sample size calculation is based on improvement in scores on the Fatigue Severity Scale (FSS). According to similar published articles [33], the FSS scores after inventions are 20.66 ± 4.54 and 40.36 ± 9.58, *n* = 57. According to the study, treatment can probably improve the FSS by 19.7 points. Improvement will be measured according to the same sample size of the estimation formula:
$$ n=2\left[{\left(\upmu \alpha +\mu \beta \right)}^2{\sigma}^2\right]/{\delta}^2 $$

With a type I error of 5% (*α* = 0.05) and 90% power (*β* = 0.10), the estimated required sample size is 43 participants per group. Allowing for a 20% dropout rate during the study, a minimum total of 100 participants is needed to reach the target of 43 participants per group.

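### Last observation carried forward is the only missing-data rule; when FSS changes over the 4 weeks it distorts the treatment comparison, by an amount that depends on dropout the plan does not specify

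*Protocol article*

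**What the plan says.** The Statistical analysis section gives one rule for incomplete data: "The missing data will be treated as the last carrier of observation". The wording is garbled, but LOCF is the only workable reading. The rule is not limited to any outcome, and no alternative method is named.

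The data it acts on are set out elsewhere in the protocol article:

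- FSS, the primary outcome: "primary outcomes will be measured at baseline and at the end of every week from the 1st to the 4th week" (Outcome measures). The three secondary scales (FIS, FACIT-F, SS-QOL) are taken only at baseline and the end of week 4.
- Repeated scores: "Analysis of variance will be used to repeat the measurement data" (Statistical analysis). Single comparisons use a t test or a non-parametric test.
- Analysis sets: intention-to-treat and per-protocol. "The results of the ITT analysis will be compared with those of the PP analysis to determine if they are consistent".
- Dropout: "Allowing for a 20% dropout rate during the study, a minimum total of 100 participants is needed" (Sample size). No split by arm or by week is given.
- Withdrawals: "The researchers will keep detailed records of why and when the subjects quit the study" (Study endpoints).

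**The concern.** LOCF assumes that a patient's fatigue stops changing on leaving. The trial expects the opposite: the Sample size section attributes a large FSS improvement to treatment, and both arms receive conventional rehabilitation for 4 weeks. A patient last seen at week 1 is therefore entered at week 4 with a score that is probably too high. If one arm loses more patients, or loses them earlier, that error does not cancel. The trial may then report a difference that does not exist, or miss or exaggerate one that does.

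The choice is fixed in the text, so it is not a detail left to a separate analysis plan. Comparing intention-to-treat with per-protocol results does not test it, because that comparison changes who is analysed and leaves the assumption about missing scores untouched.

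**Working it through.** The plan gives no figure for LOCF bias or for type I error under dropout, so there is nothing of its own to reproduce. The size has to be worked out under assumptions.

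**Inputs from the protocol article**

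- 50 patients per arm; FSS at baseline and weeks 1 to 4.
- SDs of 4.54 and 9.58 (Sample size), giving a root-mean-square SD of √[(4.54² + 9.58²)/2] = √56.19 = 7.50.
- 20% dropout during the study.

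**Assumptions the article does not give**

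- Between-visit correlation 0.7, a linear FSS fall, and dropout unrelated to the scores.
- Last observed visit equally likely to be week 1, 2 or 3.
- The split of dropout between arms, and the size of the fall in each arm.
- A true effect of 5 points. This is close to the 5.24 points that 43 per group can detect with 90% power, two-sided, at SD 7.5: √[2 × (1.960 + 1.282)² × 56.19 / 43] = 5.24.

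**Formula.** If the total fall is F, a patient last seen at week k is carried forward too high by F × (1 − k/4). Averaged over k = 1, 2, 3 this is F × (0.75 + 0.50 + 0.25)/3 = 0.5F. With dropout fraction d, the bias in active minus sham is

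0.5 × (d_active × F_active − d_sham × F_sham).

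Lower FSS is better, so a positive bias counts against active treatment. If timing differs by arm, the factor 0.5 differs by arm, and equal dropout rates no longer cancel under the null.

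**No true effect** (error rates by simulation, two-sided t test on the LOCF week-4 score)

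| Dropout active / sham | Fall in both arms | Bias | Type I error |
|---|---|---|---|
| 20% / 20% | 10 | 0.5 × (2 − 2) = 0 | about 5% |
| 30% / 10% | 0 | 0 | about 5% |
| 25% / 15% | 10 | 0.5 × (2.5 − 1.5) = 0.5 | about 6% |
| 30% / 10% | 10 | 0.5 × (3 − 1) = 1.0 | 9–10% |
| 10% / 3.3% | 10 | 0.5 × (1.0 − 0.33) = 0.33 | 5–6% |

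Swapping the arms reverses the sign. The last row spreads the 20% evenly over the 12 weeks of treatment plus follow-up, so 20% × 4/12 = 6.7% leave before week 4, with the same 1:3 imbalance.

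**True 5-point benefit** (falls of 15 active, 10 sham)

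| Dropout active / sham | Bias | Estimated benefit | Power |
|---|---|---|---|
| none | 0 | 5.0 | about 91% |
| 20% / 20% | 0.5 × (3 − 2) = 0.5 | 4.5 | about 79% |
| 6.7% / 6.7% | 0.5 × (1.0 − 0.67) = 0.17 | 4.8 | – |
| 30% / 10% | 0.5 × (4.5 − 1) = 1.75 | 3.25 | about 52% |
| 10% / 30% | 0.5 × (1.5 − 3) = −0.75 | 5.75 | – |

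**Repeated-measures comparison and the alternative.** A second set of runs used correlation 0.6 and allowed the last observed visit to be baseline, so the factor becomes (1 + 0.75 + 0.50 + 0.25)/4 = 0.625. With 30% / 10% dropout, a 10-point fall and no true effect, the bias is 0.625 × (3 − 1) = 1.25. Type I error is about 12% for the t test and about 12% for the group-by-time test in the repeated-measures ANOVA. A likelihood-based repeated-measures analysis of the observed scores, with the covariance taken as known, had null bias within 0.06 points and error of 4.1% to 5.9% across the SD 7.5 settings. That holds for data missing at random.

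**Secondary scales.** With only a baseline and a week-4 value, the last observation of any dropout is the baseline, so the change is entered as exactly zero.

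**The case against.** The strongest reply is that the harm is conditional and may be small. Much of that stands.

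- **Unequal dropout alone is not enough.** FSS must also change over time, or timing must differ by arm. With no trend, or with equal dropout and no true effect, there is no inflation.
- **Dropout before week 4 may be well under 20%.** The 20% is for the whole study, which includes 8 weeks of follow-up after the last FSS. Data collection and management also provides ward visits, recall and telephone contact to complete assessments. At about 7% the null inflation is nearly invisible.
- **No passage gives dropout by arm.** The 10% v 30% split is a stress case.

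Several stronger readings are tempting, but the documents do not support them:

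- A reader might take 19.7 points as the fall expected in both arms, which at 10% v 30% dropout gives about 21% type I error (simulated with a 20-point fall). The article derives 19.7 as the gap between two post-treatment means and uses it as the between-group difference. It nowhere assumes that sham falls by that much.
- A reader might call the withdrawal reasons in Study endpoints arm-related. They could be, but the article does not say so, and stimulation is sham-controlled and blinded.
- A reader might see the exclusion "Patients with incomplete clinical data and poor compliance" as contradicting intention-to-treat. It stands in the eligibility list, and nothing shows that it is applied after randomisation.
- A reader might say that LOCF understates uncertainty here. The calculations do not show this: error stays near 5% under equal dropout, so the inflation comes from bias.

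What the reply does not remove is the loss when a real effect exists. Equal dropout still shrinks the estimate in the cases calculated, and the direction under unequal dropout cannot be known in advance, so LOCF cannot be defended as conservative.

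**Conclusion.** The point holds in conditional form. LOCF is fixed as the sole missing-data rule for an outcome expected to change during treatment. It biases the week-4 difference and the repeated-measures comparison when dropout rate or timing differs by arm, towards or against active treatment according to which arm loses more patients. It also distorts a true effect under equal dropout.

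The size runs from negligible (about 7% lost before week 4) to material (20% lost before week 4, and more so if unevenly). All magnitudes rest on the assumed correlation, linear trajectory, falls and dropout pattern. The article names no single primary time point, so the week-4 contrast is my reading of the main comparison; the group-by-time test is affected in the same way. For FIS, FACIT-F and SS-QOL the zero-change consequence follows directly from the visit schedule and needs no simulation.

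**What to change.** For FSS, replace LOCF and the repeated-measures ANOVA with a mixed model for repeated measures on the observed weekly scores, in all randomised patients. Include treatment, week, treatment by week and baseline FSS, with an unstructured covariance, and report the week-4 contrast. Keep LOCF at most as a sensitivity analysis. Add one sensitivity analysis that departs from missing-at-random; the withdrawal reasons and dates already to be recorded can inform it. Stop applying the carry-forward sentence to the secondary scales.

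The cost is a change of wording and slightly more analysis work, best made before unblinding. Weekly FSS is already collected, so no visits are added, and the model can be fitted in SPSS, the software the plan names. The downside is that the model relies on missing-at-random, which may fail if patients leave because of unrecorded worsening; the added sensitivity analysis is there to address that.

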### Objectives and hypotheses

The objectives of this randomized controlled trial are as follows:
To study the efficacy of tDCS in combination with conventional rehabilitation;To evaluate the safety of tDCS stimulation in patients with PSF; andPresentation of the research plan and the results of previous clinical trials to ensure compliance with previously recommended guidelines.

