### Trial design

The clinical study is a prospective, randomized controlled trial designed with double-blinded assessments. Since there is no clinically effective treatment, we will perform the superiority test. This study will be carried out with 100 hospitalized patients with PSF. All participants will be randomly allocated to either the intervention or control group in a 1:1 ratio. Each group will, therefore, be composed of 50 patients. Interventions in both parallel groups were identical except for effective tDCS treatment. The control group will receive conventional rehabilitation combined with sham tDCS treatment, whereas the intervention group will receive conventional rehabilitation combined with active tDCS treatment. This trial will be composed of a 4-week intervention and an 8-week follow-up period. From the first to the fourth week, the primary outcome Fatigue Severity Scale (FSS) will be measured at baseline on every weekend. The secondary outcomes Fatigue Impact Scale (FIS), Functional Assessment Chronic Illness Therapy (Fatigue) (FACIT-F), and Specialized Quality of Life Scale in Stroke (SS-QOL) will be performed at the end of the intervention period. Adverse events and untoward effects will be supervised in each treatment. The first affiliated Hospital of Nanchang University (NCU), which will undertake the study, is responsible for training rehabilitation therapists on the standard operating procedure and supervising the progress of this trial at all clinical sites. In addition, the randomization and blinding will be performed by an independent statistician from the Center of Evidence Based Medicine, NCU. A flow diagram of this trial is presented in Fig. 1.

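### Safety is an objective, but the only comparison fixed for adverse events is a chi-square or Fisher test, whose non-significant result could not by itself support a safety conclusion with 50 patients per group

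*Protocol article*

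**What the plan says.** Protocol article, Objectives and hypotheses, lists as an aim "To evaluate the safety of tDCS stimulation in patients with PSF". The abstract also gives safety as a purpose.

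The analysis for that aim is one sentence under Statistical analysis: "Adverse events will be listed and analyzed using either a chi-square test or Fisher’s precision test". The same section says that discrete measures are summarised as percentages. The article gives no risk difference, confidence interval or upper limit for adverse events, and no expected event rate.

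The size of the trial comes from the primary outcome. Sample size works from FSS values ("the FSS scores after inventions are 20.66 ± 4.54 and 40.36 ± 9.58") and concludes that "the estimated required sample size is 43 participants per group". Trial design then states: "Each group will, therefore, be composed of 50 patients". It also frames the trial as a superiority comparison: "Since there is no clinically effective treatment, we will perform the superiority test".

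Adverse events are assessed at every treatment (Outcome measures). The ethics committee considers serious events (Safety assessments), and an independent monitoring committee oversees the trial. Data collection and management refers to a predetermined statistical analysis plan, which is not shown.

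**The concern.** A test of difference can show that active stimulation causes more adverse events. When it is not significant, it does not show that the excess is small; that needs an estimate with an interval. In a trial sized for another outcome, a non-significant result may simply reflect too few events.

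At stake is how the safety objective is answered. If the reported result is only a p-value above 0.05, readers cannot tell a small excess risk from one of 20 percentage points or more.

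**Working it through.** **The plan's own figure.** There is none for safety. The 43 per group concerns FSS only and is not used below. (The printed formula with the stated values gives 2 × (1.960 + 1.282)² × 9.58² / 19.7² ≈ 5 per group with the larger SD and 2 with the smaller, so 43 does not reproduce. That is a separate matter.)

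**Inputs**
- 50 patients per group (Trial design). Dropouts are kept in the denominator because events are recorded at each treatment.
- Two-sided α of 0.05. The protocol states 5% for FSS; two-sidedness and use for adverse events are assumptions.
- Adverse event rates: not given, so a range is assumed.

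**Step 1: chance of missing a true difference.** Let X (active) and Y (sham) be independent binomial counts with n = 50. Then

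P(miss) = Σₓ Σᵧ Bin(x; 50, p₁) · Bin(y; 50, p₀) · 1[p-value(x, y) ≥ 0.05],

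summed over all tables, for the two-sided Fisher test and the uncorrected chi-square test.

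| Sham vs active rate | Ratio | Fisher misses | Chi-square misses |
|---|---|---|---|
| 5% vs 10% | 2 | 94% | 86% |
| 10% vs 20% | 2 | 81% | 70% |
| 15% vs 30% | 2 | 65% | 56% |
| 20% vs 40% | 2 | 49% | 41% |
| 30% vs 60% | 2 | 17% | 12% |
| 5% vs 15% | 3 | 76% | 61% |
| 8% vs 24% | 3 | 51% | 38% |
| 10% vs 30% | 3 | 36% | 27% |
| 15% vs 45% | 3 | 11% | 8% |

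**Step 2: where a miss is more likely than not.** Solving P(miss) = 0.5 for the sham rate gives:
- doubling: about 17% (chi-square) and just under 20% (Fisher);
- tripling: about 6% (chi-square) and 8% (Fisher).

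**Step 3: what an interval adds.** Suppose 10 of 50 active and 5 of 50 sham patients have an event. Fisher's p is 0.26. The Wilson limits are 11.2% to 33.0% and 4.3% to 21.4%. The Newcombe interval for the 10-point difference is then
- lower: 10 − √[(20 − 11.2)² + (21.4 − 10)²] ≈ −4 points;
- upper: 10 + √[(33.0 − 20)² + (10 − 4.3)²] ≈ +24 points.

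The test reports no significant difference; the interval shows that an excess of up to about 24 points is not excluded. With 5 of 50 versus 0 of 50, Fisher's p is 0.056 and the Newcombe interval is 0.9 to 21.4 points.

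**Step 4: no events in the active group.** The exact two-sided 95% upper limit for 0 of 50 is 1 − 0.025^(1/50) = 7.1%.

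**The case against.** The best reply is that nothing in the sentence is wrong. Listing adverse events and comparing them by chi-square or Fisher is ordinary practice, and interval formats are often left to a statistical analysis plan, which this protocol mentions. Percentages per group are already planned, and the ethics committee and monitoring committee also watch over safety. In the abstract the authors themselves caution that chance cannot be excluded in a trial of this size.

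Much of this stands. Safety is not left to the test alone, and the unseen plan may contain intervals. But oversight protects patients and trial conduct; it does not supply an estimate for the objective. Nor is the protocol silent: it chooses an inferential method for a stated objective, and that method's likely result at low event rates cannot answer it.

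Three stronger readings are tempting but unsupported:
- **That the authors will take a non-significant result as proof of safety.** No section states such a rule.
- **That a doubling or tripling would usually be missed whatever the event rate.** This depends on the sham rate, which is not given. If the mild tingling mentioned in Background and rationale is recorded as an adverse event, rates could lie where the test performs reasonably.
- **That a safety margin or formal power for harm is required.** That is not normally expected for descriptive safety in a 100-patient superiority trial.

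It would also be wrong to shrink the safety groups to 40 for the planned 20% dropout, since patients who leave still contribute the events recorded before they left.

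**Conclusion.** The point holds in a limited form. The one comparative method fixed for adverse events can signal harm, but when non-significant it cannot by itself support a safety conclusion. The weakness is greatest for uncommon events: with sham rates of 5–10%, Fisher's test misses a doubling in 81–94% of trials. It fades as events become common: 10% versus 30% is missed in 27–36% of trials and 30% versus 60% in 12–17%.

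These figures rest on assumed event rates, 50 analysed patients per group and a two-sided 5% level. That a non-significant test lacks evidential value for safety does not depend on the exact rates. This is worth correcting, but it is no flaw in the efficacy design.

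**What to change.** Replace the adverse event sentence under Statistical analysis with wording such as: *For any adverse event, each type of adverse event and any serious adverse event, we will report the number and percentage of patients affected in each group and the active-minus-sham risk difference with its 95% confidence interval (for example Newcombe). Where no event occurs in the active group, the exact 95% upper limit of the rate will be given. Chi-square or Fisher p-values are descriptive, and a non-significant result will not be taken as evidence of safety.*

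If the statistical analysis plan already says this, the protocol sentence need only be aligned with it.

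The cost is a few lines of output from data already being collected; no patients, visits or margin are added. The downside is a less favourable safety statement: the report may have to say that an excess of some 20 percentage points cannot be excluded.
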